### Blinding

Participants, individuals involved in clinical decision-making and outcome assessors will be blinded to treatment allocation and will remain blinded until the database is locked. Unblinded clinicians responsible for administering active or sham treatments will draw each participant’s bedside curtain while preparing the active device. The VentFree device dims the displayed value of the stimulation current stimulation 15 s after the last current adjustment made, and the participant’s abdomen will be covered with a bed sheet so that family members, caregivers and outcome assessors are less likely to determine treatment assignments. Additionally, participants and their LAR will receive instructions not to discuss their perceptions or sensations of the treatment with others, including other participants, outcome assessors and individuals involved in clinical decision-making. This information will be reiterated a number of times during the intervention period to account for the fact patients may have been sedated/delirious at the time of enrolment.

In a case where unblinding is required, the local investigator should contact the sponsor, who can provide the site with information relating to a participant’s allocation upon reasonable request.

### Data management

Clinical data will be collected in web-based standardised electronic case report forms (eCRFs). The Food and Drug Administration (FDA) 21 CFR Part 11 and ISO14155:2020 will be followed as well as other applicable legislation on the handling of electronic data. Participant personal information will be pseudonymised. Site and participant numbers will be used to track participant information. Investigators and designated staff will receive training on eCRF completion and use of the EDC system (Viedoc, Uppsala, Sweden) prior to use.

All participant information will be kept confidential according to applicable laws and regulations. Information recorded on paper will be kept in secured locations, and electronic information will be stored on password-protected computers. The electronic data stored for this study will be kept in a database in compliance with 21 CFR Part 11, General Data Protection Regulation and the Health Insurance Portability and Accountability Act. Participant data will not contain details of participant identity. The data will be stored on a secure server and backed up routinely. Study data will be coded to prevent participant identification, except by the institution, investigators and other healthcare personnel involved in the study.

### Statistical methods

#### Competing events

Participants who die, are put on palliative care or are transferred out of the ICU for any reason due to a worsening condition before achieving successful liberation by day 28 or ICU discharge (whichever occurs first) will be considered to have experienced a competing event. The time from FES treatment administration to death, initiation of palliative care or ICU transfer due to worsening condition will be used for analysis. Participants who reach day 28, are discharged from the ICU or withdraw from the study before experiencing successful liberation from mechanical ventilation or a competing event will be considered right-censored at the earliest of day 28, ICU discharge or study withdrawal.

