### Criteria for discontinuing or modifying allocated interventions

Criteria for discontinuing or modifying allocated interventions are shown in table 1.

**Table 1 T1:** Criteria for discontinuing or modifying allocated interventions

The active or sham treatment must not be initiated if any of the following conditions are met:	Initiated treatment sessions must be paused if any of the following conditions are met:
Heart rate <50 beats per minute or >130 beats per minute	Heart rate <50 beats per minute or >130 beats per minute
Mean arterial pressure <60 mm Hg or >110 mm Hg (with or w/o vasopressors)	Mean arterial pressure <60 mm Hg or >110 mm Hg (with or w/o vasopressors)
Respiratory rate >35 breaths per minute	Respiratory rate >35 breaths per minute
SpO_2_ <90% (with ventilator support, O_2_ supplementation)	SpO_2_ <90% (with ventilator support, O_2_ supplementation)
BPS >4 or CPOT >2	Participant experiences a seizure
Participant refuses initiation of treatment	Participant requests to stop
	Increase in heart rate >20 beats per minute
	Increase in systolic blood pressure >20 mm Hg

BPS, Behavioural Pain Scale; CPOT, Critical-Care Pain Observation Tool; O2, Oxygen; SpO2, Peripheral Oxygen Saturation.

If a participant experiences a seizure during a treatment session, the session must be ended. If any of the other above-mentioned criteria are met causing the treatment to be paused, the participant should be re-evaluated every 2 min up to a maximum of 10 minutes to determine if their conditions have stabilised to within the stopping criteria parameters. If at any time during the 10-minute re-evaluation period, the participant’s parameters have returned to be within the above-mentioned criteria, the treatment can be resumed.

Participation in the trial is strictly voluntary. A participant, or their LAR, has the right to withdraw from treatment or the study at any time for any reason. The investigator also has the right to terminate the treatment or participation of a participant due to transfer to another institution, significant adverse events, any other reason relating to the participant’s safety or integrity of the trial data, participant non-compliance with the study assessments or procedures, or any problem deemed by the investigator to be sufficient to cause discontinuation from treatment or study participation. The site PI will inform the participant of the withdrawal.

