#### Secondary outcomes

Key secondary outcomes are CPF (minimum 24 hours post-extubation once the patient meets awakening criteria^13 34^) and MEP (minimum 24 hours post-extubation once the patient meets awakening criteria^13 34^). The best (maximum value) of three attempts will be used in the analyses of each individual parameter.^34^ The full pulmonary function testing protocol is provided in online supplemental appendix C.

Other secondary outcomes are:

Incidence of device-related adverse events (hospital discharge).Time from first administration of the VentFree intervention to ICU discharge.Time from first administration of the VentFree intervention to hospital discharge.Incidence of successful liberation from mechanical ventilation (day 28 or ICU discharge, whichever comes first).Incidence of reintubations (ICU discharge, 90 days post treatment).Incidence of readmissions to the ICU (90 days post treatment).Incidence of readmissions to the hospital (90 days post treatment).Incidence of acute respiratory infections (hospital discharge).Incidence of hospital-acquired infections (hospital discharge).Incidence of tracheostomy (ICU discharge).Mortality (hospital discharge, 90 days post treatment).Maximum inspiratory pressure (minimum 24 hours post extubation once the patient meets awakening criteria).Mobility as assessed by the ICU Mobility Scale^35^ (ICU discharge).Quality of life as assessed by the 5-level EQ-5D version (EQ-5D-5L)^36^ (90 days post treatment).

The full schedule of assessments is shown in the participant timeline in figure 2.

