### Sample size

Assuming an outcome expected subdistribution hazard ratio (active/sham) of 1.7, 1:1 group allocation, a type I error rate of 5% (two-sided), and 90% power, the targeted total number of participants successfully liberated from mechanical ventilation is 150. Based on the results of pilot studies, it is estimated that at least 55% of participants will achieve successful liberation. Thus, approximately 272 participants will be needed for the trial. The trial will continue to randomise participants until 150 events from the combined study groups have occurred, regardless of the total number of participants randomised. The final analysis will be performed after all randomised participants have completed or discontinued their participation in the study.

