#### Primary outcome

Cumulative incidence competing risk (CICR) estimates will be used to describe rates of successful liberation over time in the presence of a competing event. CICR curves from different treatment groups will be compared by Gray’s test at a two-sided significance level of 0.05.^37^

In the rare event that successful liberation occurs before the first VentFree treatment and any competing events, the participant will be considered as having experienced the event of interest on day 1. If any competing event occurs before both the first VentFree treatment and the event of interest, the participant will be considered as having experienced the competing event on day 1. If a participant drops out of the trial before receiving the first VentFree treatment for any reason other than successful liberation or competing events, the participant will be treated as censored on day 1.

As a supplement to the primary analysis, the cause-specific hazard ratio (*csHR*) and subdistribution hazard ratio (*subHR*) for successful liberation, accompanied by their corresponding CIs, will be computed using Cox proportional hazard model and Fine-Gray subdistribution hazard model, respectively. Robust (sandwich) variance estimators clustered by site will be used in these regression-based models to account for potential within-site correlation in this multicentre trial.

The primary analysis of the primary outcome will be based on the intent-to-treat (ITT) population, which will include all randomised participants, regardless of whether or not abdominal FES is received. Sensitivity analyses will be performed using the modified ITT population, which will include participants who receive at least one VentFree intervention session, and the per protocol population, which will include participants who receive treatment and have no major protocol deviations. In the case of any discrepancies in the conclusions derived from analyses based on different analysis populations, additional analyses will be performed to elucidate these significant differences. No interim analysis is planned.

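### Right-censoring at ICU discharge removes mainly patients who leave still ventilated, so estimated liberation is inflated and the primary comparison is biased if such discharges differ by arm

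*Protocol article*

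**What the plan says.** Under Statistical methods, Competing events, the protocol article sorts patients without successful liberation into two groups. Death, palliative care and being "transferred out of the ICU for any reason due to a worsening condition" are competing events. Everyone else in that position is censored: "Participants who reach day 28, are discharged from the ICU or withdraw from the study before experiencing successful liberation" or a competing event are right-censored at the earliest of those three times.

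The primary test uses these data: "CICR curves from different treatment groups will be compared by Gray’s test at a two-sided significance level of 0.05" (Statistical methods, Primary outcome).

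Three other places bear on the rule:

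- Outcomes, Primary outcome: a disconnected patient who stays off invasive ventilation until ICU discharge is already a success, even if 7 days have not passed.
- Interventions: ICU discharge includes leaving for an outside facility. Nothing requires the patient to be off the ventilator.
- Secondary outcomes: "Incidence of successful liberation from mechanical ventilation (day 28 or ICU discharge, whichever comes first"), so a patient who leaves the ICU unliberated counts as not liberated.

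The sensitivity and supportive analyses described change the analysis population, the time origin or the definition of liberation. None changes the handling of ICU discharge.

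**The concern.** Cumulative incidence estimation and Gray's test require that a patient censored on a given day has the same future chance of liberation as those still under observation. Here, censoring at ICU discharge depends on the outcome state. Patients off the ventilator at discharge are events, and patients on it are censored. Leaving on a ventilator is plausibly a sign of slower weaning, so the estimator credits these patients with liberations they are less likely to have.

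Two inconsistencies follow. The same departure is a competing event if it is attributed to worsening and a censoring if it is not, so a judgement by site staff decides the analysis. The primary curves and the secondary incidence outcome also treat the same patients differently and can disagree by construction.

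The rule governs the only primary test, and that test is the gate for cough peak flow and maximum expiratory pressure in the fixed sequence.

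**Working it through.** **1. The plan's own figure.** The Sample size section gives "Assuming an outcome expected subdistribution hazard ratio (active/sham) of 1.7, 1:1 group allocation, a type I error rate of 5% (two-sided), and 90% power", and states that "the targeted total number of participants successfully liberated from mechanical ventilation is 150". Schoenfeld's formula with 1:1 allocation is events = 4(1.960 + 1.282)² / (ln 1.7)² = 42.03 / 0.2816 = 149.3, so 150. With 55% liberated, 150 / 0.55 = 272.7, against about 272 stated. Both figures reproduce. The censoring rule does not enter this formula, so changing it moves neither number.

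**2. Mechanism.** The estimate is F(28) = Σ S(t−)·d(t)/Y(t), where d(t) is liberations on day t, Y(t) the number at risk and S(t−) the proportion so far free of any event. Censoring a ventilated patient lowers Y(t) on every later day, but no later d(t) was going to come from that patient. The later terms are too large, and more so when much of the liberation comes after the discharges or when deaths have thinned the risk set.

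**3. Assumed inputs (not in the article).** Share discharged ventilated; death or palliative care in 25%, scaled down on active in proportion to non-liberation when there is an effect; liberation times exponential with mean 7 days; ventilated discharges spread over days 8–23. Those discharged ventilated are taken as not liberated by day 28, the least favourable case for the current rule. Each simulated trial has 272 patients (1,500 trials without an effect, 800 with). A Fine–Gray score test with censoring weights stands in for Gray's test.

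**4. No treatment effect, true day-28 liberation 55% in both arms.**

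| Discharged ventilated, sham v active | Estimated liberation, current rule | Rejection, current rule | Rejection, counted as not liberated |
|---|---|---|---|
| 5% v 5% | 56% v 56% | 5.1% | 4.9% |
| 10% v 10% | 57% v 57% | 4.6% | 4.8% |
| 15% v 15% | 59% v 59% | 4.9% | 5.0% |
| 0% v 15% | 55% v 59% | 6.0% | 4.7% |
| 0% v 31% (10% deaths; extreme) | 55% v 67% | 11.3% | 4.5% |

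Counting these patients as not liberated returns 55% in every row. The simulation error on a 5% rejection rate is √(0.05 × 0.95 / 1500) = 0.6 points, so 6.0% alone is weak evidence. The mean test statistic in that row is 0.29, however, and Φ(−1.96 + 0.29) + Φ(−1.96 − 0.29) = 0.047 + 0.012 = 6.0%. In the extreme row the mean is 0.74, and the same sum is 11.5%.

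**5. True effect, liberation 45% on sham and 1 − 0.55^1.7 = 64% on active.**

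| Discharged ventilated, sham v active | Power, current rule | Power, counted as not liberated |
|---|---|---|
| 15% v 10% | 84% | 85% |
| 22% v 5% | 77% | 85% |
| 7.5% v 15% | 90% | 86% |

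The 85% should not be compared with the planned 90%. The simulated arms share one timing distribution, so the hazard ratio starts near 0.638/0.451 = 1.41 and is below 1.7 for much of the period. Only the contrast within a row matters.

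**6. Range.** The overstatement depends on timing and deaths. At 5–15% discharged ventilated, with discharge on days 10–24, it runs from about 0 points (early liberation, no deaths, 5%) to about 8 (nearly flat liberation, 25% deaths, 15%). With no effect and 5.7% v 14.9% discharged ventilated, the spurious gap runs from about 1 to about 6 points.

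**The case against.** The affected group is narrow. Worsening transfers, deaths and palliative care are already competing events, and patients off the ventilator at discharge are already successes. The article does not say how many remain. This stands, and it is why the size can be given only as a range.

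A reader might infer that those censored are known weaning failures. The documents do not support that. They are known to be unliberated on leaving the ICU, and some may be weaned elsewhere before day 28. If their prospects equalled those of patients who stay, there would be no bias.

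A reader might also infer that the rule threatens a false positive result. With equal shares the type I error is essentially kept. If the device works and fewer active patients leave ventilated, the bias runs toward no effect. A false positive needs more ventilated discharges on active. Blinding of clinical decision-makers and stratification by country work against transfer practice or use of the worsening label differing by arm. This stands too. What remains is inflated curves, a possible loss of power, and a comparison that depends on an unreported imbalance.

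Finally, the investigator may "terminate the treatment or participation of a participant due to transfer to another institution", from which a reader might infer that stopping treatment also leads to censoring. It does not. The discontinuation section separates treatment from participation, and the censoring rule refers to study withdrawal. No rule on stopped treatment needs repair here.

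Counting every ventilated discharge as non-liberation also has a bias of its own, named under the fix.

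**Conclusion.** The point holds for patients who leave the ICU still invasively ventilated and not labelled as worsening. Their censoring depends on the outcome, conflicts with the secondary incidence outcome, and is not varied in any sensitivity analysis described. Censoring at day 28 is administrative and is no problem.

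The likely damage to the test is modest unless ventilated discharges differ substantially between arms. The estimated curves, by contrast, are inflated even when shares are equal. All sizes rest on assumed shares discharged ventilated, on assumed timing and death rates, and on these patients not being liberated by day 28. To the extent that some are, the bias is smaller.

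**What to change.** Before unblinding, adopt one of two rules for any ICU discharge while still invasively ventilated, whatever the stated reason:

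- count it as a competing (non-liberation) event; or
- keep the patient at risk and unliberated to day 28.

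Retain the current rule as a sensitivity analysis, and report ventilated discharges by arm. The reason for transfer then no longer decides how a ventilated departure is handled.

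**Cost.** This is a wording change with no effect on the event target or sample size. A few patients weaned elsewhere before day 28 would count as not liberated, which agrees with the secondary incidence outcome.

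The two options differ in side effects. The Key secondary outcomes section imputes the worst observed value after a competing event, so the first option would also move these patients from multiple imputation to worst-value imputation for cough peak flow and maximum expiratory pressure. The first option also leaves the supplementary cause-specific hazard ratio as it is now, because that model drops patients at a competing event just as it does at censoring. The choice should be made with both in view.

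The Trial status section expected analysis to begin in April 2026. If allocation is already known, the alternative should be presented as a sensitivity analysis and labelled as added after unblinding.

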#### Primary outcome

Cumulative incidence competing risk (CICR) estimates will be used to describe rates of successful liberation over time in the presence of a competing event. CICR curves from different treatment groups will be compared by Gray’s test at a two-sided significance level of 0.05.^37^

In the rare event that successful liberation occurs before the first VentFree treatment and any competing events, the participant will be considered as having experienced the event of interest on day 1. If any competing event occurs before both the first VentFree treatment and the event of interest, the participant will be considered as having experienced the competing event on day 1. If a participant drops out of the trial before receiving the first VentFree treatment for any reason other than successful liberation or competing events, the participant will be treated as censored on day 1.

As a supplement to the primary analysis, the cause-specific hazard ratio (*csHR*) and subdistribution hazard ratio (*subHR*) for successful liberation, accompanied by their corresponding CIs, will be computed using Cox proportional hazard model and Fine-Gray subdistribution hazard model, respectively. Robust (sandwich) variance estimators clustered by site will be used in these regression-based models to account for potential within-site correlation in this multicentre trial.

The primary analysis of the primary outcome will be based on the intent-to-treat (ITT) population, which will include all randomised participants, regardless of whether or not abdominal FES is received. Sensitivity analyses will be performed using the modified ITT population, which will include participants who receive at least one VentFree intervention session, and the per protocol population, which will include participants who receive treatment and have no major protocol deviations. In the case of any discrepancies in the conclusions derived from analyses based on different analysis populations, additional analyses will be performed to elucidate these significant differences. No interim analysis is planned.

For supportive purposes, time from the start of invasive mechanical ventilation to successful liberation during the treatment period of 28 days, or ICU discharge, whichever comes first, will be analysed in the same manner as the primary outcome on the ITT population. In addition, an analysis using an alternative definition of successful liberation will be conducted, defined as disconnection from mechanical ventilation without the need for invasive mechanical ventilation within 48 hours following disconnection, or until ICU discharge, whichever occurs first. All statistical methods described for the primary analysis, including CICR estimation, Gray’s test, and the Fine-Gray subdistribution hazards model and cause-specific Cox proportional hazards model, will be applied in the same manner using the same analysis populations.

Treatment effect heterogeneity across sites and geographic regions will be assessed using Fine-Gray subdistribution hazards models including treatment-by-site and treatment-by-region interaction terms. To ensure model stability, sites enrolling fewer than 10 participants will be pooled with other small sites within the same country for the site-level analysis.

Exploratory subgroup analyses based on selected baseline demographic and clinical characteristics will also be conducted. Interaction terms will be evaluated using Fine–Gray models, and subgroup-specific estimates will be reported descriptively. Given that some subgroups may include limited numbers of participants or events, results will be interpreted cautiously and considered hypothesis-generating rather than confirmatory.

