### Sequence generation

Participants will be considered enrolled in the study once they or their LAR have signed the informed consent form, passed the screening eligibility test, met all eligibility criteria for the study and are randomised to a treatment assignment. A web-based electronic database capture (EDC) system will be used to randomly assign participants in a 1:1 ratio to active or a sham treatment. Randomisation will be stratified by country, with varying block sizes. Prior to trial initiation, an independent statistician who is not involved in the clinical aspects of the trial will generate the randomisation schedule. Randomisation will be requested by a suitably qualified local investigator for each participant. Randomisation sequences will be concealed within the EDC, with only an independent statistician having access to the allocation schedule.

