#### Key secondary outcomes

The key secondary outcomes—CPF and MEP measured when the participant meets the awakening/comprehension criteria but no sooner than 24 hours after the patient has been extubated—outcome will be sequentially compared between treatment groups using the ITT population in a superiority manner, provided that the active group demonstrates superiority over the sham group in the primary outcome. Each comparison will be conducted at a one-sided significance level of 0.05 using an unpaired t-test. The Wilcoxon rank-sum test will be performed as a supportive analysis to account for any potential violations of the normality assumption.

To control the family-wise type I error, the testing procedure will be carried out in a fixed sequence, starting with the primary outcome, followed by CPF and MEP. The testing will stop at the first rejection failure. This fixed sequence testing procedure guarantees that the family-wise error rate is appropriately controlled across both the primary and key secondary outcomes. Missing data for the key secondary endpoints will be imputed. For participants who have experienced competing events, the worst observed value for that parameter during the study will be imputed. For other participants, under the assumption of missing at random, a linear regression model (multiple imputation) will be used to impute the missing values for CPF and MEP. Predictors in the imputation model will include the following baseline factors: region, race, ethnicity, age, gender, BMI, COPD (yes/no), sepsis (yes/no), clinical frailty scale, steroid use (yes/no) and the Sequential Organ Failure Assessment (SOFA) score. Predictors may be removed if convergence issues arise.

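### Randomisation is stratified by country, but the primary and key secondary comparisons are described without country; this can cost some power and does not threaten validity

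*Protocol article*

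**What the plan says.** All references are to the Protocol article.

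- **Sequence generation:** "Randomisation will be stratified by country, with varying block sizes". The four countries are the USA, France, the Netherlands and Australia.
- **Statistical methods, Primary outcome (test):** "CICR curves from different treatment groups will be compared by Gray’s test", two-sided at 0.05. No strata are named.
- **Statistical methods, Primary outcome (models):** the cause-specific and subdistribution hazard ratios "will be computed using Cox proportional hazard model and Fine-Gray subdistribution hazard model, respectively". No country stratum or covariate is named. On variance, "Robust (sandwich) variance estimators clustered by site will be used in these regression-based models".
- **Statistical methods, Primary outcome (heterogeneity):** geography enters the models only through "Fine-Gray subdistribution hazards models including treatment-by-site and treatment-by-region interaction terms".
- **Key secondary outcomes:** CPF and MEP are compared "using an unpaired t-test". Region, age, gender, BMI, SOFA score and other baseline factors appear only as predictors in the imputation model.
- **Sample size:** "Assuming an outcome expected subdistribution hazard ratio (active/sham) of 1.7, 1:1 group allocation", two-sided 5%, 90% power, 150 liberations, about 272 participants. There is no allowance for differences between countries.

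**The concern.** Stratified randomisation balances the arms within each country. If country predicts time to liberation, a test that ignores it compares arms in a mixed population. The pooled effect is then pulled towards the null, and the variance used by the test is too large for the balance achieved, so the test becomes conservative. Analysing by the randomisation stratum removes this.

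The geographic provisions already in the plan do not do the same job. Site-clustered variances change the standard errors of the supplementary hazard ratios; they do not stratify the comparison and do not apply to Gray's test. The interaction models ask whether the treatment effect differs by place, which is a different question.

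The design has almost no reserve: 150 events give 90.1% power. Testing also follows a fixed sequence, so a missed primary outcome closes off CPF and MEP. For those two outcomes, baseline factors are judged informative enough to impute missing values but are left out of the comparison itself.

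**Working it through.** **1. The plan's own figure.** Schoenfeld's formula with hazard ratio 1.7, 1:1 allocation, two-sided 5% and 90% power:

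events = (1.960 + 1.282)² / (0.25 × ln(1.7)²) = 149.3, rounded up to 150.

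Power at 150 events is 90.1%. Participants: 150 / 0.55 = 272.7, against about 272 stated. Both figures reproduce. The formula has no country term, so analysing by country does not change the target.

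**2. Simulation inputs.** From the documents: subdistribution hazard ratio 1.7, 55% liberation overall, 28-day window, two-sided 5%, and at most 45% of participants outside the USA. Assumed, because the documents do not give them: the country mix (USA and three others at 55/20/15/10%, or 80/10/6/4%), the country liberation rates, a common treatment effect, proportional subdistribution hazards, and censoring only at day 28. Country sizes were rounded to even numbers; for the first mix 150 + 54 + 42 + 28 = 274, giving about 151 events.

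Country log-hazards relative to the USA were +s, −s and +s, so the largest ratio between two countries is exp(2s): 1.5 at s = 0.2, 2.2 at 0.4, 4.1 at 0.7 and 9.0 at 1.1. Gray's test was computed as the subdistribution log-rank test, keeping participants with a competing event at risk to day 28, with and without country strata.

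**3. Power.** There were 40,000 runs per row, and 6,000 in the two rows marked *.

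| Mix | Sham day-28 liberation across countries | Unstratified | Stratified | Loss (points) |
|---|---|---|---|---|
| 55/20/15/10 | 46% in all | 0.9025 | 0.9010 | −0.15 |
| 55/20/15/10 | 38-51% | 0.8992 | 0.8994 | 0.0 |
| 55/20/15/10 | 32-57% | 0.8930 | 0.9022 | 0.9 |
| 55/20/15/10 | 23-66% | 0.8705 | 0.8998 | 2.9 |
| 55/20/15/10 | 15-78%* | 0.8085 | 0.8935 | 8.5 |
| 55/20/15/10 | USA 27%, others 72%* | 0.8088 | 0.9002 | 9.1 |
| 80/10/6/4 | 39-52% | 0.8988 | 0.8980 | −0.1 |
| 80/10/6/4 | 33-58% | 0.8984 | 0.9013 | 0.3 |
| 80/10/6/4 | 25-68% | 0.8855 | 0.8975 | 1.2 |

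The Monte Carlo standard error of one power figure is about 0.15 points at 40,000 runs: √(0.9 × 0.1 / 40,000) = 0.0015.

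**4. Type I error.** With hazard ratio 1.0 and 6,000 runs, the unstratified test rejected in 0.050, 0.047 and 0.045 of trials for s = 0.2, 0.4 and 0.7, and in 0.024-0.028 at the two extremes. With no country difference, both tests came out slightly high (0.058 unstratified, 0.057 stratified). That was chance: a repeat with 40,000 runs gave 0.050 for both. In the same longer repeat the unstratified test gave 0.048, 0.047, 0.039 and 0.026 for s = 0.2, 0.4, 0.7 and 1.1, while the stratified test stayed at 0.050-0.051.

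**5. CPF and MEP.** The documents give no standard deviations or covariate correlations for these outcomes, so the gain from adjustment was not computed.

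**The case against.** **The test may be stratified after all.** The article never uses the word unstratified, and its analysis plan, which is not shown, may name strata for Gray's test. This stands as a limit on confidence. It does not dispose of the point: the article sets out clustered variances, interaction terms and a pooling rule for small sites, yet gives country no role in the main comparison. Nor does it reach the t-test, which has no country or covariate term by construction.

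**Power is lost whenever country rates differ.** A reader might infer this, but the figures do not bear it out. The loss is nil for mild differences, and about 3 points needs roughly a fourfold spread in subdistribution hazard. No document gives country rates, and the common weaning protocol is meant to reduce variation in practice.

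**The primary test is invalid.** A reader might infer this too. It is not supported: ignoring the stratum makes the test conservative. An unpaired t-test is likewise valid in a randomised trial.

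**Stratifying is not free.** This stands in part. Non-US enrolment is capped at 45%, about 122 of 272, over three countries with no minimum each. In the 80/10/6/4 mix the smallest country has about 11 participants (0.04 × 272) and about 6 liberations (11 × 0.55). The estimate also becomes a within-country effect. A pooling rule deals with the first; the second needs stating.

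**The t-test change is unquantified.** This stands. Participants with a competing event receive the worst observed value, so how much baseline covariates would sharpen the comparison is unknown.

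**Conclusion.** The mismatch between randomisation and analysis is in the text and is worth correcting, as a matter of efficiency and consistency. It does not put the trial's conclusions at risk of a false positive.

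Leaving country out of Gray's test costs between nothing and about 3 points of power across mild to large country differences, and 8-9 points only at extremes. With 80% of participants in the USA, the mild-to-large range shrinks to about 0 to 1.2 points. Stratified power stays near 90% throughout. All these sizes rest on the assumed mixes and rates, a common proportional effect and censoring at day 28 only. Confidence is high for the t-test wording and moderate for Gray's test and the models, where the conclusion rests on what the article does not say.

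**What to change.** Before database lock and unblinding, and with the change dated and documented:

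1. Name a country-stratified Gray's test as the primary test, with a prespecified rule for pooling very small countries.
2. Stratify the Fine-Gray and cause-specific Cox models by country under the same rule, keeping the site-clustered variances.
3. Compare CPF and MEP with a linear model containing arm, country and prespecified baseline covariates already collected, for example age, gender and BMI.
4. Keep the unstratified Gray's test, the unstratified models and the t-test as sensitivity analyses.
5. State that the treatment effect is then a within-country effect.

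If the analysis plan already stratifies, the article should say so; if the unstratified test is deliberate, the reason should be given.

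The cost is plan wording and small programming changes, at most about 0.2 points of power if countries do not differ, and possible pooling of sparse strata. The 150-event target and the number of participants are unchanged. Time is short: the Trial status section puts the end of recruitment in January 2026 and the start of analysis in about April 2026.
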